**6.3 Statistical Methods**

The statistical analyses for the efficacy and demographic variables are described below. Unless otherwise stated, all hypothesis tests will be conducted using a two-sided α=0.1 (one-sided α=0.05) level of significance.

**6.3.1 Analysis of Baseline and Demographic Characteristics**

Baseline and demographic characteristics of the safe population will be summarized by treatment group and overall. Continuous variables will be summarized via the mean, median, standard deviation, minimum, maximum, and number of nonmissing observations. Categorical variables will be summarized via counts and percentages. The Chi-squared test or Fisher's exact test for categorical parameters and the t-test for continuous parameters will be applied to compare the two intervention groups. The results will be presented as the number of patients (%) or mean ± standard deviation (SD). P<0.05 is defined as statistical significance.

**6.3.2 Analysis of Primary Variables**

The primary endpoint is the identification rate of the SLNs, defined as the number of patients who had at least one SLN detected divided by the total number of patients included. Quantitative variables will be expressed as percentages. The 95% confidence interval will be calculated.

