**4. RANDOMIZATION TO THE TREATMENT ARM**

The participating investigators will be responsible for ensuring that each new patient fulfills the study inclusion criteria, is informed appropriately about the study, reads and understands the patient information sheet and dates and signs the informed consent form for participation in the study.

An interactive response system will be used to achieve treatment assignment. A randomization sequence will be created with a 1:1 allocation. Randomization envelopes, numbered with sequential subject IDs, will be prepared by the research office personnel. Each envelope will contain a card identifying the test type assigned to that subject ID. The randomization envelopes will be maintained in a secure fashion in the research office.

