**6.3.5 Determination of Sample Size**

The sample size for the study is based on the primary endpoints. The non-inferiority (one-sided) hypothesis is adopted, which assumed an SLN identification rate of 96% for each group^79^ and a non-inferiority margin (∆) of 6% to secure an identification rate above 90% (one-sided test significance level (α) =0.05). A sample size of 264 patients was required to give a power of 80% to reject the null hypothesis that the identification rate in the UC group is inferior to that of the GC group by more than a 6% non-inferiority margin (with a 5% probability of type I error). Anticipating a 10% dropout rate, at least 294 patients will need to be recruited.

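### The 95% confidence interval for the primary endpoint is not tied to the one-sided 5% non-inferiority test or to the 6-point margin; as a two-sided criterion it would give about 70–75% power, not 80%

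*Protocol*

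**What the plan says.** **Test level.** Section 6.3 states that, unless otherwise stated, "all hypothesis tests will be conducted using a two-sided α=0.1 (one-sided α=0.05) level of significance". The sample-size text (section 6.3.5, repeated in the Synopsis) uses the same level: "one-sided test significance level (α) =0.05".

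**Sizing.** Section 6.3.5 "assumed an SLN identification rate of 96% for each group", sets a margin of 6 percentage points, and concludes: "A sample size of 264 patients was required to give a power of 80% to reject the null hypothesis". It then adds: "Anticipating a 10% dropout rate, at least 294 patients will need to be recruited". Allocation is equal (section 4: "A randomization sequence will be created with a 1:1 allocation").

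**Primary analysis.** Section 6.3.2 defines the identification rate, says that results are given as percentages, and ends: "The 95% confidence interval will be calculated". It mentions no difference between arms, no test, no margin and no success criterion. The margin appears only in the sample-size text.

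**The concern.** Non-inferiority is commonly concluded by comparing one limit of the interval for the difference with the margin. The only interval the protocol names for the primary endpoint is a 95% one. Read in the usual two-sided sense, its lower limit corresponds to a one-sided level of 0.025, not the 0.05 used for sizing and testing. The opening qualifier in section 6.3 adds doubt, since an analyst could take 6.3.2 as the stated exception. Sections 6.3.1 and 6.3.3 already depart from the general level by using P<0.05 for baseline and secondary comparisons.

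At stake is the trial's single confirmatory claim. The study is unmasked (section 4.1). If the deciding bound is not written down, it could be chosen once the results are visible. If the two-sided 95% limit is chosen, the stated power is not what the trial delivers.

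**Working it through.** **Inputs (Protocol 6.3.5 and 4):** rate 0.96 in each arm; margin 0.06, taken as an absolute difference (0.96 − 0.06 = 0.90, the floor that the protocol names); one-sided alpha 0.05; power 80%; 1:1 allocation; 264 patients (132 per arm); 10% dropout; 294 recruited (147 per arm).

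**1. Reproduce the stated size.** With an unpooled variance:

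n per arm = (z₁₋α + z₀.₈₀)² × 2 × 0.96 × 0.04 / 0.06²

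For one-sided 0.05: (1.645 + 0.842)² × 0.0768 / 0.0036 = 131.9, so 132 per arm and 264 in total. Dropout: 264 / 0.90 = 293.3, so 294. Both figures match the protocol.

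**2. Power under each bound.** Power = Φ(0.06 / SE − z), with SE = √(0.0768 / n).

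| Evaluable | SE | 0.06 / SE | Two-sided 90% limit (z = 1.645) | Two-sided 95% limit (z = 1.960) |
|---|---|---|---|---|
| 264 (132 per arm) | 0.02412 | 2.487 | 80.0% | 70.1% |
| 294 (147 per arm) | 0.02286 | 2.625 | 83.6% | 74.7% |

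Exact binomial enumeration with Wald limits agrees: 80.4% and 71.0% at 132 per arm; 84.4% and 76.1% at 147 per arm. Any result that passes on the 95% limit also passes on the 90% limit. Under the design assumptions the two limits therefore disagree in about 9% of trials at 132 per arm (80.4 − 71.0) and about 8% at 147 per arm (84.4 − 76.1).

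**3. A result on which they disagree.** UC 139/147 = 94.56%; GC 141/147 = 95.92%; difference −1.36 points. Wald SE = √(0.9456 × 0.0544/147 + 0.9592 × 0.0408/147) = 0.0248.

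- Two-sided 90% lower limit: −1.36 − 1.645 × 2.48 = −5.4 points, above −6: passes.
- Two-sided 95% lower limit: −1.36 − 1.960 × 2.48 = −6.2 points, below −6: fails.

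**4. Size needed if a two-sided 95% limit were to decide with 80% power.** (1.960 + 0.842)² × 0.0768 / 0.0036 = 167.4, so 168 per arm, 336 evaluable; 336 / 0.90 = 373.3, so 374 recruited.

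**5. Side calculation for a score-type bound.** Exact enumeration with Farrington-Manning limits at one-sided 0.05 gives 74.6% power at 132 per arm and 78.5% at 147 per arm. This matters only if such a method is chosen.

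**The case against.** The strongest reply is that the protocol does not contradict itself. It gives one test level, one-sided 0.05, in every place where it mentions the primary hypothesis. Section 6.3.2 states no other level. Coming straight after the remark about percentages, its interval can be read as one for each arm's rate. Reporting a two-sided 95% interval beside a one-sided 5% test is ordinary practice, and a one-sided 95% bound would match the sizing exactly. This stands. A reader might infer that two decision rules coexist, but the text supports only one test level and an interval with no role assigned to it.

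It also stands that the power loss needs three unwritten steps: the interval is two-sided, it is for the difference, and it is what is compared with the margin. The 70% figure applies to 264 evaluable patients. Section 3 speaks of up to 294 evaluable subjects, for which the figure is about 75%. On that reading the criterion is also stricter than planned, so the cost is lost power rather than a greater risk of a false non-inferiority claim.

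A reader might further infer that the stated 5% type I error is not held, because 264 reproduces with an unpooled Wald-type formula and exact enumeration of a 90% Wald limit at 90% v 96% with 132 per arm gives 6.1%. The documents do not support this as an error. They prescribe no Wald analysis, a sizing formula does not bind the analysis, and the interval method is a detail that an analysis plan may settle.

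The reply does not remove the mismatch. The protocol did not leave the interval level to another document. It fixed 95% for the primary endpoint and did not connect it to the test, the difference or the margin.

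**Conclusion.** The point holds as an ambiguity in the primary analysis with a conditional loss of power. In its usual two-sided sense, the only interval written for the primary endpoint does not match the alpha behind the stated 80% power, and nothing in section 6.3.2 says which bound decides.

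If the one-sided 0.05 level governs, the sizing is correct and power is 80% with 264 evaluable patients. If a two-sided 95% interval for the difference governs, power is about 70% with 264 and about 75% with 294. These figures assume true rates of 96% in both arms, an absolute 6-point margin and the normal approximation; exact Wald enumeration is within about 1.5 points of them.

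**What to change.** State one rule in section 6.3.2: non-inferiority is concluded if the lower limit of the two-sided 90% confidence interval (equivalently, the one-sided 95% bound) for the difference in identification rate, UC minus GC, exceeds −6 percentage points; any two-sided 95% interval is descriptive. This keeps the level already used in 6.3 and 6.3.5. It costs one sentence and no patients.

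If the sponsor means a two-sided 95% interval to decide, say so and restate the power in 6.3.5 and the Synopsis as about 70% (264 evaluable) to 75% (294 evaluable). Holding 80% under that rule would take about 336 evaluable patients, or 374 recruited at 10% dropout.

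Optional, and not a correction of an error: if a score method (Farrington-Manning or Miettinen-Nurminen) is chosen for the one-sided 0.05 bound, the power statement should give about 75% with 264 and about 79% with 294.

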**6.3.3 Analysis of Secondary Variables**

The chi-squared test or Fisher's exact test for categorical parameters and the t-test for continuous parameters will be applied to compare the two intervention groups. The results will be presented as the mean ± standard deviation (SD). P<0.05 is defined as statistical significance.

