**STUDY DESIGN**

This study is a single-centre, open-label, randomized controlled, non-inferiority, phase 3 trial. The patients will be randomly assigned (1:1) using a permuted block randomization scheme to receive either ultrasound-assisted CNS (UC group) or CNS plus ICG dual-tracer-guided (GC group) SLN mapping.

UC group=ultrasound-assisted CNS for SLN mapping. GC group=dual-tracer method using CNS plus ICG for SLN mapping. DCIS=ductal carcinoma in situ. ALND=axillary lymph node dissection. CNS=carbon nanoparticle suspension. ICG=indocyanine green.

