**1.1.4 Ultrasound-guided Surgery**

ICG and RI are able to provide deep insight into the SLNB location prior to skin incision. However, when the CNS technique is used alone for SLNB, it depends on the surgeon's naked-eye observation and experience, which may prolong the duration of surgery. Therefore, locating black-stained lymph nodes during surgery still requires improvement.

An easily available and feasible method to improve the amount of healthy breast tissue spared while ensuring tumor-free resection margins is intraoperative ultrasonography (US). US-guided surgery enables the surgeon to visualize the tumor during excision. Previous studies have clearly shown the efficacy of US-guided surgery for nonpalpable tumors. Rahusen et al. reported that US-guided surgery, during which an experienced radiologist performed the US, is superior to wire-guided surgery with respect to tumor-free resection margins (89% and 55% of cases, respectively). Snider et al. also showed an excellent rate of tumor-free resection margins using USS (82%) with a smaller volume of healthy breast tissue resection compared to wire-guided surgery (62.2 cm^3^ and 81.1 cm^3^, respectively)^69-74^.

Previous anatomical studies have revealed that the SLNs are neither evenly nor randomly distributed in the axilla but are instead located in predetermined anatomical regions. K.B. Clough et al. found that the SLNs in 86.8% of breast cancer patients were located in the area adjacent to the lateral thoracic tributary of the axillary vein (LTV), extending from the lower border of the axilla to the second intercostobrachial nerve (ICBN), and, more noticeably, 98.2% of SLNs were found in the medial part of the axilla, alongside the LTV, regardless of the site of the primary tumors^75^. These results are consistent with a previous autopsy study in which 87% of axillary SLNs were located between the lateral border of the pectoralis major muscle and the thoracoepigastric vein^76^. Considering the close proximity between the LTV and the lateral border of the pectoralis major muscle^76-68^, the present study used the lateral border of the pectoralis major muscle as a convenient surface landmark for the localization of axillary SLNs.

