**3.1 Inclusion Criteria**

Patients meeting all of the following inclusion criteria by the end of the screening phase should be considered for admission to the study:

1. The patient must be female and 18 years of age or older.

2. Resectable invasive adenocarcinoma of the breast, confirmed histologically.

3. Ductal carcinoma in situ confirmed by histologically scheduled mastectomy.

4. The patient must have preoperative clinical Tis and T1, T2, T3, M0 breast cancer.

5. Without clinical or radiological nodal involvement (cN0): no positive ipsilateral axillary lymph nodes; no prior removal of ipsilateral axillary lymph nodes; no suspicious palpable nodes in the contralateral axilla or palpable supraclavicular or infraclavicular nodes, unless proven nonmalignant by biopsy.

6. Clinically positive lymph nodes (cN1) (including any abnormal or enlarged clinically palpable lymph nodes or core biopsy/surgical biopsy/FNA evidence of malignant cells within any lymph nodes) were downstaged to cN0 following neoadjuvant therapy.

7. The patient must have an ECOG performance status of Grade 0-1.

8. The patient must provide written informed consent before participating in the study.

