**5. PATIENT TREATMENT**

**5.1 Preoperation Chemotherapy**

Standard neoadjuvant therapy before randomization will be performed according to the NCCN guidelines and clinical practice.

Evaluation of neoadjuvant chemotherapy (every 2 cycles):

- Breast and axillary ultrasound (every 2 cycles)
- Mammogram (first plus one before surgery)
- Breast MRI (first plus one before surgery)

Quality control of SLNB after neoadjuvant therapy entails removal of the clip-containing node and at least 3 lymph nodes. Intraoperative radiography will be used to identify the clipped node.

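### The secondary comparisons of operative duration and metastatic rate are fixed as unadjusted tests, which are valid but give up some precision that baseline factors known at entry could supply

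*Protocol*

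**What the plan says.** Section 6.3.3 prescribes the tests for the secondary endpoints: chi-squared or Fisher for categorical variables and, for the rest, "the t-test for continuous parameters will be applied to compare the two intervention groups". It adds that "P<0.05 is defined as statistical significance". No covariate is named there or elsewhere.

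The Study Design section says that patients are "randomly assigned (1:1) using a permuted block randomization scheme", and names no stratification factor.

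The population is mixed by design. Section 3.1 admits DCIS scheduled for mastectomy, invasive cancer, cN0 patients, and cN1 patients downstaged to cN0 by neoadjuvant therapy. On T category it says: "The patient must have preoperative clinical Tis and T1, T2, T3, M0 breast cancer".

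Section 5.1 places neoadjuvant therapy before randomisation. After it, the clipped node and no fewer than three nodes must be removed, and "Intraoperative radiography will be used to identify the clipped node". Section 6.3.3 measures operative duration from skin incision to removal of the sentinel node specimens. Both operative duration and metastatic rate are restricted to patients in whom a sentinel node was found.

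**The concern.** Two baseline facts are in hand before allocation. Neoadjuvant status must be known because Section 4.1 limits the interval from the last chemotherapy cycle to randomisation. Clinical T category must be known because it is an eligibility item.

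Neoadjuvant status plausibly predicts operative duration, because the extra nodes and the search for the clip can fall between incision and specimen removal. Neoadjuvant status and T category also plausibly predict whether a sentinel node is positive. A crude test leaves that explainable variation in the error term, so intervals for the arm difference are wider than they need be.

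There is also a practical side. Section 6.3.1 plans significance tests of baseline characteristics but gives no rule for acting on them. If neoadjuvant share happened to differ between arms, any adjustment would be chosen after the data were seen and would be open to challenge. Naming the covariates now removes that discretion.

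**Working it through.** **The plan's own figure.** Section 6.3.5 "assumed an SLN identification rate of 96% for each group", with a 6-point margin, one-sided α = 0.05 and 80% power.
- n per arm = (1.645 + 0.842)² × 2 × 0.96 × 0.04 / 0.06² = 131.9, so 132 per arm and 264 in total.
- Dropout: 264 / 0.90 = 293.3, so 294.

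Both figures reproduce. They concern the primary endpoint only and do not change below.

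**Inputs for the secondary endpoints.** About 96% of 132, that is 127 per arm, would have a sentinel node found. The two-sided level is 0.05, from Section 6.3.3, which overrides the general rule in Section 6.3. The protocol gives no SD of duration, neoadjuvant share or positivity rate. These are assumed over ranges.

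**Operative duration.**
- Unadjusted detectable difference at 80% power: (1.960 + 0.842) × √(2/127) = 0.352 SD.
- If covariates explain a share R² of the variance, the standard error is multiplied by √(1 − R²). Power for the same 0.352 SD is Φ(2.802/√(1 − R²) − 1.960).

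| R² | SE multiplier | Fall in SE | Power |
| --- | --- | --- | --- |
| 0% | 1.000 | none | 80% |
| 5% | 0.975 | 2.5% | 82% |
| 10% | 0.949 | 5% | 84% |
| 20% | 0.894 | 11% | 88% |
| 30% | 0.837 | 16% | 92% |

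To see which R² neoadjuvant status alone might give, take a share s and a shift in mean time of d within-group SDs: R² = s(1 − s)d² / (1 + s(1 − s)d²).
- s = 20%, d = 0.5: 0.04/1.04 = 4%.
- s = 30%, d = 1: 0.21/1.21 = 17%.
- s = 40%, d = 1.5: 0.54/1.54 = 35%.

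**Metastatic rate.** Take one binary factor with share s, positivity p1 with it and p0 without it, and overall rate p = s·p1 + (1 − s)·p0. The variance ratio of the adjusted to the crude risk difference is [s·p1(1 − p1) + (1 − s)·p0(1 − p0)] / [p(1 − p)]. Example with s = 30%, 45% versus 20%: p = 0.275, and 0.18625/0.19938 = 0.934, so the SE multiplier is 0.967.

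| Positivity with / without the factor | Fall in SE, s = 10% | Fall in SE, s = 30% |
| --- | --- | --- |
| 30% / 20% | 0.3% | 0.6% |
| 45% / 20% | 1.6% | 3.3% |
| 60% / 15% | 6% | 11% |

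**Are the crude tests still valid?** With 132 per arm under simple randomisation, the between-arm difference in a factor of prevalence p has SD √(2p(1 − p)/132). That is 3.7 points at p = 10% and 6.2 at p = 50%, so 95% ranges are about ±7 to ±12 points.

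Trials with no arm effect were then simulated: 127 per arm, 10,000 trials per setting, factor share 10% or 30%, shift 0.5 or 1 SD for time, and positivity 45% versus 20%.
- Type I error at nominal 5% was 4.5-5.3% for the t-test and 4.7-5.1% for the chi-squared test.
- Mean bias of the crude difference in time was about zero.
- Adjustment cut the standard error for time by 1-9%, for example from 0.1400 to 0.1269 at share 30% and shift 1 SD.

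**The case against.** The strongest reply is that a t-test and a chi-squared test are valid in a randomised trial without stratification, that they match the design, and that adjustment is often left to a statistical analysis plan, which is not shown. The point about validity stands in full. The point about the analysis plan stands in part. Section 6.3.3 does not rule out further adjusted analyses, but it does positively prescribe the crude tests as the comparison of the arms, so a later plan with an adjusted main comparison would depart from it.

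The size of the gain cannot be derived from the protocol. That also stands, which is why only ranges are given.

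A reader might infer three stronger things that the protocol does not support.
- *That chance imbalance undermines these comparisons.* It can move the estimate in one particular trial: an 11-point imbalance with a 1-SD shift moves the time difference by 0.11 within-group SD, about 0.8 of its standard error (0.11/0.14). But the crude standard error already allows for this, as the simulation shows.
- *That the protocol itself names stage and neoadjuvant therapy as drivers of these endpoints.* T category appears only as an entry criterion. The effect of neoadjuvant therapy on time is inferred from Section 5.1, which does not say that the extra steps lengthen the measured interval. The axillary response range of 23-74% in Section 1.1.1 does not compare positivity between patient types.
- *That surgeon is an available covariate.* Section 1.1.4 speaks of "naked-eye observation and experience, which may prolong the duration of surgery", but about carbon nanoparticles used alone, which is neither arm. Nothing says that the operating surgeon is recorded or fixed at randomisation, and surgery may follow up to 14 days later (Section 4.1). No gain from adjusting for surgeon is therefore claimed.

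**Conclusion.** The point holds as a question of efficiency. Section 6.3.3 fixes crude tests although neoadjuvant status and clinical T category are known before allocation and are plausibly prognostic. For operative duration, an assumed R² of 5-30% gives a standard error lower by 2.5-16% and power of 82-92% where the crude test has 80%. For metastatic rate the fall is 0.3-11%, and it is probably small unless positivity differs sharply between patient types.

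The stated tests are neither invalid nor biased, and the non-inferiority conclusion and the 264/294 sample size are untouched. Adjustment would not fully repair the restriction of both endpoints to patients with a sentinel node found, which is a separate matter. This is a free improvement on secondary endpoints.

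**What to change.** Amend Section 6.3.3 as follows.
- **Operative duration:** the main comparison is a linear model with arm and neoadjuvant therapy (yes/no). Add operating surgeon only if the surgeon is recorded and assigned before randomisation.
- **Metastatic rate:** the main comparison is a Mantel-Haenszel or standardised risk difference, adjusted for neoadjuvant therapy and preoperative clinical T category as recorded at entry. State whether that category is the one before or after neoadjuvant therapy. With T grouped as Tis, T1 and T2-T3, crossing with neoadjuvant status gives up to six strata, so give a rule in advance for collapsing sparse ones.
- **Crude tests:** keep the t-test and the chi-squared or Fisher test as supportive analyses.

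The cost is a paragraph of wording, to be settled before any outcome data by arm are examined. Neoadjuvant status and T category are needed for entry anyway. Surgeon would need an extra recorded item if it is not already collected.
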